## Abstract

**Background:**

Immigrant women’s challenges in realizing sexual and reproductive health and rights (SRHR) are exacerbated by the lack of knowledge regarding how to tailor post-partum contraceptive services to their needs. Therefore, the overall aim of the IMPROVE-it project is to promote equity in SRHR through improvement of contraceptive services with and for immigrant women, and, thus, to strengthen women’s possibility to choose and initiate effective contraceptive methods post-partum.

**Methods:**

This Quality Improvement Collaborative (QIC) on contraceptive services and use will combine a cluster randomized controlled trial (cRCT) with a process evaluation. The cRCT will be conducted at 28 maternal health clinics (MHCs) in Sweden, that are the clusters and unit of randomization, and include women attending regular post-partum visits within 16 weeks post birth. Utilizing the Breakthrough Series Collaborative model, the study’s intervention strategies include learning sessions, action periods, and workshops informed by joint learning, co-design, and evidence-based practices. The primary outcome, women’s choice of an effective contraceptive method within 16 weeks after giving birth, will be measured using the Swedish Pregnancy Register (SPR). Secondary outcomes regarding women’s experiences of contraceptive counselling, use and satisfaction of chosen contraceptive method will be evaluated using questionnaires completed by participating women at enrolment, 6 and 12 months post enrolment. The outcomes including readiness, motivation, competence and confidence will be measured through project documentation and questionnaires. The project’s primary outcome involving women’s choice of contraceptive method will be estimated by using a logistic regression analysis. A multivariate analysis will be performed to control for age, sociodemographic characteristics, and reproductive history. The process evaluation will be conducted using recordings from learning sessions, questionnaires aimed at participating midwives, intervention checklists and project documents.

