## Introduction

Globally, as compared to native-born women, immigrant women across countries of all income groups report lower access to contraceptive services, accompanied by higher rates of unintended pregnancies and abortions [1–4]. A plethora of barriers to accessing contraceptive services exist for immigrants, such as language challenges, various cultural and religious beliefs, strict gender roles, social pressure and financial factors [5, 6]. Additionally, despite variation across immigrant populations, their family planning knowledge is generally low, causing misconceptions about contraceptive methods and limiting their possibilities to prevent unintended pregnancies [7–9].

Immigrants’ contraceptive decision making is further influenced by migration status, changes or instabilities in living conditions, and adaptation to resettlement communities [10–12]. While immigrants post resettlement might employ using contraceptives to regain financial and social stability, barriers to contraceptive services still exist [12–15].

With this said, there is a paucity of research regarding immigrants and post-partum contraception use. Ensuring access to effective post-partum contraception is fundamental when seeking to reduce inequities that immigrants face in SRHR, as it prevents unintended pregnancies, abortions and enables birthspacing [16]. A short interpregnancy interval (IPI) – less than 12 months – increases the risk of complications, e.g., preterm birth, low birthweight, stillbirth and neonatal death [17, 18]. Use of more effective post-partum contraception, such as long-acting reversible contraception (LARC) (i.e. intrauterine devices) and short-acting reversible contraception (SARC) (i.e. oral contraceptive pills), supports birth-spacing and prevents unintended pregnancies, abortions as well as pregnancy-related adverse events [19]. What little evidence exists regarding immigrants’ post-partum contraceptive use highlights that immigrant women are less likely to plan or attend post-partum clinic visits and use reliable contraception methods in a timely manner compared to non-immigrants, sometimes despite their interest [20–22].

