Several quality improvement collaboratives (QICs) have been applied to improve obstetric, gynaecological and neonatal care, although many lacked close user engagement [37–41]. There is also promising evidence of how the umbrella of community-based participatory research (CBPR) and co-design methods are being employed to address health disparities and improve SRHR services for immigrants [42–44]. Co-design in healthcare involves HCPs, patients, caregivers, designers and researchers working together as equal partners to improve specified health outcomes and system efficiency [45]. Therefore, QICs based on the Breakthrough Series Collaborative model and co-design methods can help organizations to make and sustain measurable improvement according to patients needs, as well as stimulate joint learning and networking among HCPs [46].

In Sweden, a few small-scale QICs have demonstrated the importance and effectiveness of increasing user engagement. The evaluations of these QICs report positive results when seeking to improve access to or choice of effective methods in the context of abortion or post-partum care [40, 41, 47]. The lack of studies similar to these reflect how little evidence exists on how to combine QICs and co-design methods to improve immigrants’ post-partum contraceptive services.

Therefore, the overall aim of IMPROVE-it is to promote equity in SRHR through the improvement of contraceptive services and, thus, to strengthen women’s possibility to choose and initiate effective contraceptive methods post-partum. The hypothesis is that focusing on the following three evidence-based areas of change regarding contraceptive services:1) developing tools to share information about contraceptive methods’ effectiveness,2) developing approaches to providing CC and3) improving access to contraceptive methods (Fig. 1) will lead to a significant increase in immigrant women’s choice and use of effective contraceptive methods.

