### Self-administered questionnaire

Inclusion criteria: Women 18 years and above coming for post-partum visits within 16 weeks post birth (live birth).

Exclusion criteria: Women who do not anticipate becoming sexually active with a male partner within six months.

Midwives at intervention and control clinics will invite women to participate in the study, i.e. respond to a digital or printed paper questionnaire during the visit and be contacted for follow-up six and 12 months post enrolment. There is also the possibility to participate in a telephone interview with an interpreter. Additional information will be provided at the MHCs before prospective participants give their written, digital or verbal informed consent.

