#### cRCT

The SPR will be used to retrieve the primary outcome, women’s choice of contraception, and covariates for evaluating social determinants such as age, sociodemographic characteristics and reproductive history. To evaluate secondary outcomes regarding participants’ satisfaction with the contraceptive counselling received, women attending the post-partum visit will complete a questionnaire that utilizes the Person-Centered Contraceptive Counseling Measure-scale (PCCC-scale) [65]. Participating women will also receive a follow-up questionnaire six and 12 months after the postpartum visit to evaluate their ongoing contraceptive use and satisfaction with the contraceptive method. In addition, the follow-up questionnaire will ask about unintended or planned pregnancy, induced abortion and miscarriages since the post-partum visit (Table 1).

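### Entry to the primary analysis depends on a visit made after clinic randomisation, under consent wording that differs by arm, so randomisation alone does not secure a causal comparison

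*Protocol article*

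**What the plan says.** - **Who is in the trial.** The Abstract (Methods) says the cRCT will "include women attending regular post-partum visits within 16 weeks post birth". Clinics are the unit of randomisation. Allocation is reported as done, and the intervention runs in 2022–2023.
- **Where the outcome comes from.** Under *cRCT*: "The SPR will be used to retrieve the primary outcome". *Eligibility of MHCs and inclusion criteria* has intervention clinics register the choice at the post-partum visit. The outcome itself is timed from birth, up to 16 weeks.
- **Consent.** The same section commits control clinics to register the choice of women who consent. It attaches no consent condition to registration at intervention clinics.
- **Analysis.** *Statistical analysis* takes all women in the cRCT as the population and relies on the randomisation scheme for a causal estimate.
- **Denominator.** *Power analysis and randomisation* counts an average of 100 participants per clinic and glosses them as pregnant women.
- **Attendance.** The Introduction reports that "immigrant women are less likely to plan or attend post-partum clinic visits" and names "improving access to contraceptive methods" as one of three areas of change.
- **Questionnaire.** *Self-administered questionnaire* states: "Midwives at intervention and control clinics will invite women to participate in the study, i.e. respond to a digital or printed paper questionnaire". It excludes "Women who do not anticipate becoming sexually active with a male partner within six months".

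**The concern.** Randomising clinics balances, in expectation, the women those clinics serve. It does not balance the women who later come to a post-partum visit if the allocation can influence who comes. Here attendance is both the condition for entry and the occasion on which the outcome is recorded. The article describes attendance as selective, and the intervention has a component that could plausibly affect it. If the extra women brought in choose effective methods less often than usual attenders, the comparison is tilted against the intervention. If they come because they want a method, it is tilted in favour.

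The consent wording adds a second route. Read literally, the control arm contributes consenting women and the intervention arm contributes all attenders. Adjustment for age, sociodemographic characteristics and reproductive history cannot be counted on to remove selection on unmeasured willingness to use contraception.

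**Working it through.** **1. The plan's own figure.** Inputs from *Power analysis and randomisation*: ICC 0.05, 100 women per clinic, 15-point difference, α 0.05. Two-sided testing and equal allocation (14 clinics per arm) are assumed. The control rate is not given.
- Design effect: 1 + (100 − 1) × 0.05 = 5.95.
- Effective size per arm with 28 clinics: 14 × 100 / 5.95 = 235.3.
- Noncentral t with 26 df and control rates of 0.35 to 0.50: power 88.6% to 89.3%. With 30 clinics the minimum is 90.8%.

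The stated 88% and 90% are reproduced to within 2 points at mid-range control rates. The calculation assumes no selection, so it neither supports nor refutes the concern.

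**2. Pregnant women or attenders.** If 100 means pregnant women and, say, 80 attend (assumed), the design effect is 1 + 79 × 0.05 = 4.95 and the effective size is 14 × 80 / 4.95 = 226.3. The loss of information is small. The mismatch matters for who is being compared, not for power.

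**3. Selection through attendance, true effect zero.** All rates are assumed, because the article gives none. Let attendance be a0 (control) and a1 (intervention). Usual attenders choose an effective method at 50%, extra attenders at rate q.
- Rate among intervention attenders = [a0 × 0.50 + (a1 − a0) × q] / a1.
- 80% v 90%, q = 20%: (80 × 0.50 + 10 × 0.20) / 90 = 46.7%, so −3.3 points. With q = 80%: 53.3%, so +3.3.
- 70% v 85%, q = 20%: (70 × 0.50 + 15 × 0.20) / 85 = 44.7%, so −5.3. With q = 80%: +5.3.
- Standard error with 100 analysed women per clinic: √(2 × 0.25 / 235.3) = 0.0461. The two-sided 5% test then rejects in 10.7% of trials at 3.3 points and 19.8% at 5.3 points.
- A smaller shift, 80% v 85%, gives at most 1.8 points and 6.6%.

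**4. Selection through consent, in the control arm only.** If a share c consents and consenters' rate exceeds non-consenters' by d, the control rate shifts by (1 − c) × d.
- c = 80%, d = 10 points: 0.20 × 10 = 2 points, rejection 7%.
- c = 60%, d = 15 points: 0.40 × 15 = 6 points, rejection 24%.

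The shift changes sign if consenters choose effective methods less often.

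**5. How much depends on non-attenders.** Assume attendance of 75% v 85%, usual attenders at 55%, extra attenders at 30% and no counselling effect.
- Attenders: (75 × 0.55 + 10 × 0.30) / 85 = 52.1% v 55.0%, so −2.9 points.
- All women, non-attenders set to 0%: 44.25% v 41.25%, so +3.0.
- All women, non-attenders at 30% in both arms: 44.25 + 15 × 0.30 = 48.75% v 41.25 + 25 × 0.30 = 48.75%, so 0.

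The same data give −2.9, 0 or +3.0 points, depending only on what is assumed about women who did not attend.

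**The case against.** **Access to methods is not access to the visit.** The article speaks of access to contraceptive methods, and the intervention it describes consists of learning sessions, action periods and co-design workshops, with no recall or outreach. The sentence on lower attendance compares immigrant with non-immigrant women, not arms. This stands: no passage shows that attendance will differ by arm. It does not remove the risk, because nothing in the plan prevents or measures such a difference.

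**A reader might infer that the trial would penalise the intervention for succeeding, even reversing the sign.** The documents do not support this. The reversal in step 5 needs a counselling effect near zero. With the same assumed attendance and baseline rates and the planned 15-point effect, attenders give (75 × 0.70 + 10 × 0.45) / 85 = 67.1% v 55.0%, or +12.1 points. With a 5-point effect the result is 57.1%, still +2.1.

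**A reader might infer that the midwife's invitation decides who is in the primary analysis.** The article ties the invitation and the sexual-activity exclusion to the questionnaire, while the primary outcome comes from the register. As written they threaten the questionnaire outcomes directly. That inviting midwives at intervention clinics know their allocation is inferred from their consent to the QIC; it is not stated. Only the consent wording for control clinics leaves a route to the primary outcome.

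**Counting non-attenders as having no effective method has a bias of its own.** This stands. If attendance differs by arm, that coding misclassifies differentially in favour of the intervention. In step 5 it produces +3.0 points when the true difference may be zero.

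**Detailed analysis sets belong in the full protocol or SAP.** This is fair for detail. Here, however, the article itself makes statements that do not fit together: consent in one arm, pregnant women against attenders, and reliance on randomisation for a population formed after it.

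**Conclusion.** The concern holds as a risk of unknown direction. Entry to the primary analysis and recording of its outcome both depend on a visit made after clinics were allocated, and the randomisation scheme alone does not support a causal reading among attenders. The one-sided consent wording and the two denominators leave the primary population unclear.

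Under the assumed rates and no true effect, the spurious difference is up to 3.3 points (rejection 10.7%) or 5.3 points (19.8%) through attendance, and 2 to 6 points (7% to 24%) through consent in one arm. These sizes rest on assumed attendance, consent and choice rates, 28 clinics of 100 analysed women, and ICC 0.05. They are modest beside the planned 15 points but would matter for a smaller observed effect. The documents do not establish that bias will occur or which way it would run.

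**What to change.** 1. Define the population for the register-based primary outcome by one rule, identical in both arms. Neither questionnaire consent nor the sexual-activity exclusion should decide who is in it. Reconcile *Eligibility of MHCs and inclusion criteria*, *Power analysis and randomisation* and *Statistical analysis* with that rule.
2. Report by arm the number of women registered in pregnancy with a live birth in the window, the proportion attending, and the proportion with a recorded choice.
3. Keep the analysis of attenders. Add a prespecified sensitivity analysis in all women registered at the clinic with a live birth in the window, varying the choice rate among non-attenders from none to the attender rate and letting it differ by arm. Do not fix non-attenders at no effective method as the primary analysis.

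The cost is a wider register extract (assuming the register identifies these women whether or not they attend), some rewording, and one extra analysis that rests on assumptions about non-attenders. The intervention and the randomisation stay as they are.

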**Discussion:**

The intervention’s co-design activities will meaningfully include immigrants in implementation research and allow midwives to have a direct, immediate impact on improving patient care. This study will also provide evidence as to what extent, how and why the QIC was effective in post-partum contraceptive services.

**Trial registration:**

NCT05521646, August 30, 2022.

## Introduction

Globally, as compared to native-born women, immigrant women across countries of all income groups report lower access to contraceptive services, accompanied by higher rates of unintended pregnancies and abortions [1–4]. A plethora of barriers to accessing contraceptive services exist for immigrants, such as language challenges, various cultural and religious beliefs, strict gender roles, social pressure and financial factors [5, 6]. Additionally, despite variation across immigrant populations, their family planning knowledge is generally low, causing misconceptions about contraceptive methods and limiting their possibilities to prevent unintended pregnancies [7–9].

Immigrants’ contraceptive decision making is further influenced by migration status, changes or instabilities in living conditions, and adaptation to resettlement communities [10–12]. While immigrants post resettlement might employ using contraceptives to regain financial and social stability, barriers to contraceptive services still exist [12–15].

With this said, there is a paucity of research regarding immigrants and post-partum contraception use. Ensuring access to effective post-partum contraception is fundamental when seeking to reduce inequities that immigrants face in SRHR, as it prevents unintended pregnancies, abortions and enables birthspacing [16]. A short interpregnancy interval (IPI) – less than 12 months – increases the risk of complications, e.g., preterm birth, low birthweight, stillbirth and neonatal death [17, 18]. Use of more effective post-partum contraception, such as long-acting reversible contraception (LARC) (i.e. intrauterine devices) and short-acting reversible contraception (SARC) (i.e. oral contraceptive pills), supports birth-spacing and prevents unintended pregnancies, abortions as well as pregnancy-related adverse events [19]. What little evidence exists regarding immigrants’ post-partum contraceptive use highlights that immigrant women are less likely to plan or attend post-partum clinic visits and use reliable contraception methods in a timely manner compared to non-immigrants, sometimes despite their interest [20–22].

The antenatal and post-partum period offers room for strengthening SRHR by improving contraceptive services. One focus of such improvement efforts can include double sessions of contraceptive counseling (CC), whereby sessions occur during both the antenatal and the post-partum period, as this has shown to increase contraceptive use after giving birth [23–25].

Additionally, offering information about contraceptive methods’ effectiveness and potential side effects can counteract patient-provider power imbalances that may hinder women’s choices of contraceptive methods [26]. For example, in Sweden, structured CC (“the LOWE model” using an educational video, an effectiveness chart, four key questions, and a box with contraceptive models) increased LARC choice, initiation and use, when controlled for migration background [27]. Immigrant women in Sweden have also expressed the importance of trust in CC encounters, especially since they perceive these as private matters [28].

High-quality post-partum CC—meaning that the HCP discusses what matters most to a patient in choosing a method—occurs less often among immigrant women, who are less likely to know where to seek such services, even if they are free of charge [29, 30]. Furthermore, the needs of immigrant women may be known by HCPs, but the womens’ knowledge and values may not be properly addressed [31]. HCPs express several challenges in communicating with immigrant women regarding SRHR including navigating cultural and religious differences and patients’ distrust in healthcare [31–33]. Overall, previous studies report several opportunities for improving underutilized SRHR services by interacting with immigrant women, taking into account their experiences, and adapting one’s practice to the situation at hand [34–36].

Several quality improvement collaboratives (QICs) have been applied to improve obstetric, gynaecological and neonatal care, although many lacked close user engagement [37–41]. There is also promising evidence of how the umbrella of community-based participatory research (CBPR) and co-design methods are being employed to address health disparities and improve SRHR services for immigrants [42–44]. Co-design in healthcare involves HCPs, patients, caregivers, designers and researchers working together as equal partners to improve specified health outcomes and system efficiency [45]. Therefore, QICs based on the Breakthrough Series Collaborative model and co-design methods can help organizations to make and sustain measurable improvement according to patients needs, as well as stimulate joint learning and networking among HCPs [46].

In Sweden, a few small-scale QICs have demonstrated the importance and effectiveness of increasing user engagement. The evaluations of these QICs report positive results when seeking to improve access to or choice of effective methods in the context of abortion or post-partum care [40, 41, 47]. The lack of studies similar to these reflect how little evidence exists on how to combine QICs and co-design methods to improve immigrants’ post-partum contraceptive services.

Therefore, the overall aim of IMPROVE-it is to promote equity in SRHR through the improvement of contraceptive services and, thus, to strengthen women’s possibility to choose and initiate effective contraceptive methods post-partum. The hypothesis is that focusing on the following three evidence-based areas of change regarding contraceptive services:1) developing tools to share information about contraceptive methods’ effectiveness,2) developing approaches to providing CC and3) improving access to contraceptive methods (Fig. 1) will lead to a significant increase in immigrant women’s choice and use of effective contraceptive methods.

**Fig. 1 Fig1:**
[figure not shown]
Intervention. Quality improvement collaborative

### Research questions

How does a Quality Improvement Collaborative (QIC) combined with co-design methodology influence immigrant women’s choice of effective post-partum contraception?

How and by what mechanisms does a QIC influence contraceptive services, and how does context affect the QIC efforts and outcomes?

